# Comparison of Efficiency of Closed Kinetic Chain Exercises Versus Proprioceptive Exercises in Improving Balance and Gait in People With Hemophilia: Protocol for a Randomized Controlled Trial

**DOI:** 10.2196/66770

**Published:** 2025-04-24

**Keywords:** hemophilia A, hemophilia B, exercise, gait, postural balance, efficiency, hemophilia, proprioceptive exercises, balance, protocol, randomized controlled trial (RCT), bleeding disorder, protein deficiencies, blood clotting, quality of life, young adult, teenager

## Abstract

**Background:**

Inherited bleeding disorders involve prolonged bleeding due to clotting protein deficiencies, with hemophilia A and B being the most common types. The severity of bleeding in people with hemophilia depends on the deficient factor level. Treatment includes coagulation factor concentrates, nonreplacement preparations, gene therapies, and physiotherapy, whereby bleeding is prevented, symptoms are reduced, and the quality of life is improved. Closed kinetic chain exercises improve joint stability and neuromuscular control by stabilizing the proximal base, making them favored in musculoskeletal rehabilitation. Proprioceptive exercise training improves the sensorimotor system’s adaptability and injury prevention through tailored programs involving progressively complex movements and surfaces.

**Objective:**

The aim of this study is to investigate the effects of closed kinetic chain exercises and proprioceptive exercise training on improving balance and walking in people with hemophilia.

**Methods:**

This study is a 3-arm, parallel-group randomized controlled trial with 63 people with hemophilia aged 13-25 years who meet the inclusion criteria. The primary outcome measures are medio-lateral swing, anterior-posterior swing, walking speed, and Hemophilia Joint Health Score. Secondary outcome measures are kinematic assessment of gait, one-leg stand test, 6-minute walk distance (6MWD) test, proprioception assessment, and the Functional Independence Score in Hemophilia. Participants will be evaluated with the Biodex balance system for postural sway, 10-meters walking test for gait speed, Hemophilia Joint Health Score for joint health, Kinovea 2D motion analysis for kinematic evaluation of gait, one-leg stand test for balance measurement, 6MWD for functional capacity, digital goniometer for proprioception, and Functional Independence Score in Hemophilia for functional independence. Participants will be randomly assigned to a closed kinetic chain exercise group, a proprioceptive exercise group, or a control group. All participants in exercise training groups will receive a 30-minute education session on joint protection techniques and energy conservation prior to the first exercise session. Closed kinetic chain exercises will include progressive lower limb exercises of approximately 45 minutes each session. Proprioceptive exercise training will focus on vibration training; reposition exercises and proprioception exercises will be administered to increase proprioceptive input for the same duration as the other group. The control group will receive no intervention. All participants will undergo 24 exercise sessions (2 days a week for 12 weeks). After the treatment, the initial measurements will be repeated.

**Results:**

This study began in September 2023 and is scheduled to be completed in May 2025. A total of 34 participants have completed the study to date.

**Conclusions:**

This study will investigate the effects of 2 different exercises on functional parameters in people with hemophilia. The effects of different exercise protocols on parameters such as postural sway, walking speed, and joint health will be evaluated. It is predicted that both exercise methods may have positive effects on balance and gait.

**Trial Registration:**

Clinical Trials.gov NCT05879549; https://clinicaltrials.gov/study/NCT05879549

**International Registered Report Identifier (IRRID):**

DERR1-10.2196/66770

## Introduction

Inherited bleeding disorders are rare diseases characterized by prolonged bleeding time due to deficiencies in protein cofactors and enzymes involved in blood clotting [1]. Among coagulopathies, hemophilia A, caused by a deficiency of factor VIII, and hemophilia B, resulting from a deficiency of factor IX, are the most common [2]. The severity of hemophilia is determined by the levels of the clotting factors in the blood, and is classified as mild, moderate, or severe hemophilia [3]. In mild hemophilia, bleeding occurs due to trauma, surgical procedures, and dental intervention. In moderate hemophilia, recurrent musculoskeletal bleeding is observed. In severe cases, spontaneous bleeding is also common [1].

In people with hemophilia, the location, timing, and severity of the clinical symptoms and findings vary depending on the level of the deficient factor. Bleeding in the musculoskeletal system is the most common type of bleeding, with 70%-80% occurring in the joints and about 15% occurring in the muscles [4]. The most frequently affected joints are the knee, ankle, and elbow [2]. Recurrent hemarthroses in people with hemophilia cause hypertrophy of the synovial membrane, making the joint more susceptible to further bleeding and increasing the risk of hemophilic arthropathy [5].

Current pharmacological treatments for hemophilia include standard or extended half-life factor preparations, therapies balancing the nonfactor coagulation system, intravenous or subcutaneous applications, and gene therapies that have been licensed in recent years [5,6]. In addition to pharmacological treatment, various physiotherapy methods are applied to prevent new bleeds and alleviate existing symptoms. The goals of physiotherapy and rehabilitation are to relieve pain, increase joint range of motion, prevent muscle atrophy, improve functional ability, reduce the frequency of joint bleeds, and enhance the quality of life [7].

According to the closed kinetic chain exercise model, consecutive rigid segments are connected by intermediary segments [8]. The terminal segment is fixed in this exercise model, and body weight resistance is provided. The advantage of closed kinetic chain activities is that they create stability in the proximal segment, providing a more solid base for distal mobility or ambulation, resulting in increased joint stability and neuromuscular control [9]. Closed kinetic chain exercises have been preferred in the rehabilitation of many musculoskeletal problems over the past 20 years [8,10].

Proprioception is a neural process that includes the body’s ability to respond to sensory inputs from the environment [11]. Proprioceptive exercise training can enhance the sensorimotor system’s ability to adapt to changing environments, thereby protecting the body from injuries [12]. Proprioceptive exercise training includes various exercises tailored to the patient’s condition, focusing on transitioning from hard to softer surfaces, stable to unstable surfaces, simple to more complex movements, supported to unsupported movements, and different joint angles [13]. Sensorimotor training programs for lower extremity proprioception exercises include active joint repositioning exercises, coordination exercises, muscle performance, balance or unstable surface training, plyometric training, and vibration training [14].

Due to the frequent occurrence of hemarthroses in the lower extremity joints, changes in balance and walking parameters can be observed in people with hemophilia. A previous study has shown that the restricted rolling behavior of the foot in individuals with hemophilia, which may be caused by movement limitations and pain, can alter the balance between different foot areas [15]. Another study reported that changes in gait patterns in boys with hemophilia are associated with altered physical function performance [16].

Research [17,18] has demonstrated that both proprioceptive and closed kinetic chain exercises have beneficial effects on functional abilities in patients with lower extremity impairments. However, comparative studies evaluating the efficacy of these 2 exercise modalities specifically in people with hemophilia are yet to be conducted. This study aims to investigate the effects of closed kinetic chain exercises and proprioceptive exercise training approaches on improving balance and walking in people with hemophilia.

## Methods

### Participant Selection

The sample size was calculated as 18 individuals for each group using the G*Power program (version 3.1.9.4; Heinrich Heine University) with 90% power and .05 type 1 error using the medio-lateral swing effect size value as reference in the balance assessment in the study by Tat et al [19]. Considering that there might be individuals who would not complete the study, a total of 63 participants, that is, 21 individuals for each group, will be included.

The inclusion criteria of the participants in this study were as follows: (1) diagnosed with hemophilia A and hemophilia B, (2) have a blood factor level below 5%, (3) is 13-25 years of age, (4) have a history of bleeding in the lower extremities, (5) have a target joint, (6) have a total lower extremity Hemophilia Joint Health Score ≥3, and (7) is receiving prophylaxis (factor support to prevent bleeding). The exclusion criteria were as follows: (1) individuals having undergone lower extremity surgery in the last 6 months, (2) having BMI>30 kg/m^2^, (3) having an inhibitor, (4) using a walking aid, and (5) being involved in any physiotherapy or exercise program in the last 6 months.

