### Statistical Analysis

Data will be statically analyzed using SPSS (version 25.0; IBM Corp). Normality tests (visual and analytical) will be applied. Descriptive statistics will be presented as mean (SD) or frequency (percentage). The Shapiro-Wilk test will be used to assess the normality of data distribution. For normally distributed data, a one-way analysis of variance test will be applied for between-group comparisons, and a 2-sided paired sample *t* test will be used for within-group changes. For nonnormally distributed data, the Kruskal-Wallis test will be used for between-group comparisons, and the Wilcoxon test will be applied for within-group changes. In cases where between-group comparisons of normally distributed data show significant results, Tukey or Bonferroni corrections will be used as post hoc analyses to identify the source of the differences. For nonnormalized distributed data, Mann-Whitney *U* tests will be conducted for between-group comparisons. A *P* value <.05 will be considered statistically significant for all analyses.

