## Results

This research received funding from the Turkish Scientific and Technological Research Institution as of September 1, 2023. From this date, cases began to be incorporated into the study. By April 2025, a total of 34 participants had completed the treatment phase. Once all enrolled participants have finished their treatment, data analysis will commence. The anticipated completion date for this study is May 2025.

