Recurrent bleeding is the major factor leading to hemophiliac arthropathy. Lower extremity arthropathies may cause balance problems. A previous study [19] where static posture was evaluated using Biodex similar to our study showed that medio-lateral oscillations increased in people with hemophilia. These changes were found to be associated with the clinical scores of the lower extremity joints. That study emphasized the importance of balance assessment and suggested that exercises to enhance medio-lateral stability should be incorporated into rehabilitation programs. Although lower extremity arthropathies may affect balance scores, worse balance scores have been reported in patients with and without hemophilic arthropathy compared to healthy individuals. For this reason, we incorporated methods from the literature known to positively impact balance parameters into our study.

Exercise training is one of the most commonly recommended methods to prevent and treat musculoskeletal problems that may develop in patients with hereditary bleeding disorders [15]. Traditionally, the most commonly used exercise types are aerobic exercises, strengthening exercises, aquatic exercises, and combined training. In our study, the effectiveness of customized exercise programs will be compared differently from that in existing literature. Chronic synovitis, cartilage damage, and subchondral bone damage due to recurrent joint bleeding in people with hemophilia may decrease proprioceptive information [32]. For this reason, one of the exercise groups that we planned was based on proprioception. The effect of progressively developed sensorimotor exercises on balance and gait parameters will be revealed.

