Gönen et al [33] performed different exercise trainings for 21 patients for 12 weeks in people with hemophilia: 7 patients were included in the closed kinetic chain exercise training group, 7 in the conventional exercise group, and 7 in the control group. They concluded that closed kinetic chain exercise training was superior in proprioception and physical activity compared to conventional exercises for people with hemophilia A [33]. In our study, we aim to investigate the effects of closed kinetic chain exercises on balance and gait parameters. Additionally, by the end of the study, we will compare the outcomes of proprioceptive exercise training and those of closed kinetic chain exercises. This comparison will contribute to developing optimal exercise training programs for people with hemophilia.

Bleeding episodes induced by exercise in people with hemophilia have been reported as rare adverse events [15]. In our study, to prevent any bleeding during exercises, the exercises were scheduled on the days when patients received their factor replacement therapy.

A limitation of this study is the lack of long-term follow-up, which is particularly relevant, given that hemophilia is a chronic condition that predisposes individuals to ongoing musculoskeletal system challenges. The absence of extended outcome assessments limits the ability to evaluate the sustained effects of the exercise interventions on balance, gait, and joint health over time.

Our study will contribute to the literature as the first study comparing the protocols of closed kinetic chain exercises and proprioceptive exercises in people with hemophilia. We expect our study to be a pioneer in the future, especially in protocols that contribute to the improvement of daily life activities such as balance and walking, which are affected by bleeding.

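### The stated 90% power should not be read as power for closed kinetic chain versus proprioceptive exercise, and the 54-completer target does not fit the May 2025 end date

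*Protocol article*

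**What the plan says.** Under Participant Selection, "The sample size was calculated as 18 individuals for each group using the G*Power program", "with 90% power and .05 type 1 error using the medio-lateral swing effect size value as reference in the balance assessment" of one cited study. An allowance for non-completion raises this to 21 per group, 63 in total. The size of the effect and the test are not given.

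The Discussion describes the cited study: static posture was measured on the Biodex system, and the study "showed that medio-lateral oscillations increased in people with hemophilia". The changes were related to lower-limb joint scores, and the study recommended exercises for medio-lateral stability.

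Under Statistical Analysis, normally distributed data are compared by one-way ANOVA. If that is significant, "Tukey or Bonferroni corrections will be used as post hoc analyses". Non-normal data go to Kruskal-Wallis and Mann-Whitney tests, with no correction named.

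The title question is head-to-head, and the Discussion confirms it: "we will compare the outcomes of proprioceptive exercise training and those of closed kinetic chain exercises". The Conclusions and Discussion expect both exercises to help.

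Under Results, inclusion began on 1 September 2023. "By April 2025, a total of 34 participants had completed the treatment phase", and "The anticipated completion date for this study is May 2025". Analysis starts once all enrolled participants have finished treatment. Under Intervention, treatment lasts 12 weeks.

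**The concern.** A reader who meets 90% power in a trial titled as a comparison of two exercises will attach the 90% to that comparison. Three features of the article work against this.

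- The effect that drives the calculation comes from a study described as measuring balance, not as training anyone.
- For normal data, a pairwise claim must pass the ANOVA and then a correction over three pairs.
- If both exercises help, as the article expects, the difference between them may be a good deal smaller than the difference of either from control.

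At stake is the interpretation of a null head-to-head result, which looks more informative beside a 90% figure than the design allows. The recruitment record adds to this: if the study closes on the stated date, the analysed sample may fall well short of the one the 90% was computed for.

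**Working it through.** **Inputs from the article.** 18 per group (54 in total), power 0.90, alpha .05, three arms 1:1:1, 63 to be included, start 1 September 2023, 34 completers by April 2025, end May 2025, 12 weeks of treatment. The planning effect and test are not stated, so the effect is solved backwards.

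**1. The plan's own figures.**
- Inflation: 18 / (1 − 1/7) = 21; 21 × 3 = 63. This reproduces.
- Two-sample t test, noncentrality d√(n/2), n = 18, two-sided .05: 90% power needs d = 1.11 (1.112 × √9 = 3.34).
- One-way ANOVA, noncentrality f²N, N = 54: 90% power needs f = 0.499 (0.499² × 54 = 13.4).

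So 18 per group is a possible answer for either test, with a large effect.

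**2. Pairwise power at f = 0.50, 18 per arm, normal data.** Each pair is counted as significant only if the ANOVA is significant and the corrected pairwise test is too (simulation, 40,000 runs).

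| Pattern of means | Difference implied by f = 0.499 | ANOVA | Pairwise, Bonferroni to Tukey |
|---|---|---|---|
| Both exercises equal, control differs | f × 3/√2 = 1.06 SD for each exercise against control; head-to-head 0 | 90% | each exercise–control pair 76–78% |
| One exercise midway between control and the other | 2f√(3/2) = 1.22 SD for the widest pair; head-to-head 0.61 SD | 90% | widest pair about 88%; head-to-head 27–29% |

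If both exercises are 1.11 SD better than control, each exercise–control pair has 80–82%.

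**3. Head-to-head power for assumed differences.** The article gives no expected difference between the exercises, so these two are assumptions. Two-sample t test, 18 per arm:
- 0.5 SD: 31% at .05; 17% at .05/3.
- 0.8 SD: 65% at .05; 46% at .05/3.

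**4. Detectable head-to-head difference, 18 per arm.**
- At .05: 0.96 SD (80% power), 1.11 SD (90%).
- At .05/3: 1.13 SD (80%), 1.28 SD (90%).

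**5. Target against date.**
- Outstanding completers: 54 − 34 = 20.
- Pace: 34/20 = 1.70 to 34/19 = 1.79 a month from the start. Leaving out the first 12 weeks, in which nobody could finish, it is up to 34/16.25 = 2.09.
- Time for 20 more: 20/2.09 = 9.6 to 20/1.70 = 11.8 months.
- To finish by 31 May 2025, a participant must have started by 8 March 2025 (31 May minus 12 weeks).
- Linear projection to the end of May, one to two further months: 34 + 1.70 = 35.7 to 34 + 2 × 2.09 = 38.2, or about 36–38 completers, roughly 11–13 per arm.
- Power for 1.11 SD at 11 and 13 per arm: 70% and 78% with an unadjusted t test. After gate and correction (exercise against control, both exercises equal) it is about 54–56% and 62–65%.

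**The case against.** The strongest reply is that nothing has been miscalculated. The planned between-group test is a one-way ANOVA, 18 per group gives 90% for it at f = 0.50, and the article never claims 90% for each adjusted pair. Sizing on the omnibus test is a recognised choice. This stands: a reader might infer that the 90% is an arithmetic error, and the article does not support that.

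Four further limits also stand.

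- The loss from correction depends on the unstated test and the pattern of means. With one arm midway, the widest pair keeps about 88%. If control is the worst arm, however, that pair is exercise against control, and the head-to-head pair is the one left at 27–29%. The correction is specified only for normal data.
- It is tempting to call the planning effect a patient-versus-healthy difference. The article also reports associations with joint scores, and which contrast supplied the effect cannot be seen.
- It is tempting to measure the shortfall against 63. That is the number to be included; the completers required are 54. Likewise, 36–38 is a projection, because the number in treatment is not given and the end date is only anticipated. A shortfall lowers achieved power without making the design calculation wrong.
- No equivalence claim is planned, so an equal-effectiveness reading is a risk to forestall, not a stated intention.

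A condensed article may also leave the effect size and test to the full protocol, so their absence alone is not the point.

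**Conclusion.** The concern holds in a limited form. On the article's own description of its source, the 90% is not shown to be power for a difference between randomised arms, and it should not be read as the power of the title comparison. The size depends on assumptions: the 27–29% head-to-head figure rests on f = 0.50, one exercise midway and normal data, while the 31% and 17% rest on an assumed 0.5 SD. What does not depend on the pattern of means is the detectable difference: at 18 per arm, about 1 SD or more is needed for conventional power head-to-head.

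The published target and date do not fit together. Reaching 54 by the end of May would take 20 completions in at most two months, or at least 10 a month, against about two a month so far. Only an unusually large number already in treatment could close that gap, and none is reported.

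**What to change.** 1. Restate the 90% as applying to the test it was computed for, and say that the planning effect comes from a balance assessment and is used as a proxy for a between-arm difference.
2. Add the detectable head-to-head differences at 18 per arm, unadjusted and with Bonferroni for three pairs, as worked out above.
3. Tie the data lock to 63 randomised or 18 completers per arm and revise the completion date. If accrual has to stop, report the achieved number and its detectable difference in place of 90%.
4. State now that a non-significant head-to-head result will be reported with its confidence interval and not as equal effectiveness.

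The cost is a less favourable stated power and a later date. No patients beyond the stated target, and no change of test, are required. By the article's account, analysis starts only after all enrolled participants finish, so the wording can be settled before results are seen.

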### Ethics Approval

This study was approved by Istanbul University-Cerrahpaşa ethics committee (E-74555795-050.01.04-689576; May 3, 2023). The Declaration of Helsinki will guide this study. After eligibility is confirmed, written and verbal information about the study will be provided to all the participants. Then, the participants will sign a written informed consent form stating that they agree to participate in the research. The informed consent form also states that participation in the study is free and voluntary. No additional fees will be charged to the participants, and no payment will be made. The personal data and identity information of the participants will be kept confidential. Participants have the right to withdraw from the study at any time. The data will be used purely to contribute to science without any profit motive (Multimedia Appendix 1). At the same time, the data can be statistically analyzed without secondary approval when necessary. The trial intervention is similar to other clinical practices; therefore, we consider that risks from the trial are minimal. Additionally, exercise training approaches in the intervention group will be applied with the same protocol and duration to the participants in the control group at the end of the study.

